## Abstract

**Background:**

PHI-101 is an orally available, selective checkpoint kinase 2 (Chk2) inhibitor. PHI-101 has shown anti-tumour activity in ovarian cancer cell lines and impaired DNA repair pathways in preclinical experiments. Furthermore, the in vivo study suggests the synergistic effect of PHI-101 through combination with PARP inhibitors for ovarian cancer treatment. The primary objective of this study is to evaluate the safety and tolerability of PHI-101 in platinum-resistant recurrent ovarian cancer.

**Methods:**

Chk2 inhibitor for Recurrent EpitheliAl periToneal, fallopIan, or oVarian cancEr (CREATIVE) trial is a prospective, multi-centre, phase IA dose-escalation study. Six cohorts of dose levels are planned, and six to 36 patients are expected to be enrolled in this trial.

Major inclusion criteria include ≥ 19 years with histologically confirmed epithelial ovarian cancer, fallopian tube carcinoma, or primary peritoneal cancer. Also, patients who showed disease progression during platinum-based chemotherapy or disease progression within 24 weeks from completion of platinum-based chemotherapy will be included, and prior chemotherapy lines of more than five will be excluded. The primary endpoint of this study is to determine the dose-limiting toxicity (DLT) and maximum tolerated dose (MTD) of PHI-101.

**Discussion:**

PHI-101 is the first orally available Chk2 inhibitor, expected to show effectiveness in treating recurrent ovarian cancer. Through this CREATIVE trial, DLT and MTD of this new targeted therapy can be confirmed to find the recommended dose for the phase II clinical trial. This study may contribute to developing a new combination regimen for the treatment of ovarian cancer.

**Trial registration:**

ClinicalTrials.gov Identifier: NCT04678102.

**Supplementary Information:**

The online version contains supplementary material available at 10.1186/s12885-021-09138-z.

## Background

DNA damage repair (DDR) system impairment has been associated with ovarian cancer carcinogenesis [1]. Approximately 50% of high-grade serous ovarian cancer is associated with homologous recombination deficiency (HRD) and other DDR systems, including base excision repair, nucleotide excision repair, mismatch repair, and non-homologous end-joining system, also attributed to ovarian cancer development [1, 2]. Especially, tumours harbouring HRD showed synthetic lethality leads to higher sensitivity in poly(ADP-ribose) polymerase (PARP) inhibitors. Recent clinical trials on advanced or recurrent ovarian cancer have shown efficacy with PARP inhibitors. Olaparib increased progression-free survival in BRCA1/2 mutated patients in primary ovarian cancer [3], and niraparib prolonged progression-free survival regardless of HRD status or BRCA mutations in primary ovarian cancer [4].

Checkpoint kinase 1 and 2 (Chk1 and 2) are activated by ataxia telangiectasia mutated kinase (ATM) and ataxia telangiectasia and Rad3-related kinase (ATR) pathways, which are mainstreams of the DDR system [5]. Chk1 and 2 are activated by DNA double-strand breakage and involved in the homologous recombination (HR) pathway. ATR phosphorylates Chk1, and the function of ATR and Chk1 is essential in cell cycle regulation and the DDR system. Several Chk1 and 2 depleting agents were developed, and prexasertib, which showed higher affinity to Chk1, was one of the promising molecules [6, 7]. A phase II study of prexasertib on BRCA mutant-type recurrent ovarian cancer yielded only an 11.1% response rate and a 29% response rate in BRCA wild-type recurrent ovarian cancer [6, 8].

On the other hand, Chk2 is a serine/threonine kinase and functions as a barrier in tumorigenesis by maintaining genomic stability, and loss of Chk2 is known to be discovered in solid tumours, including ovarian cancer [9]. PHI-101 is the first oral Chk2 selective inhibitor, identified by artificial intelligence and a big data-based in-house drug discovery platform. Anti-tumour activity of PHI-101 is shown in various ovarian cancer cell lines, including CAOV3, OVCAR3, and SC-OV3. PHI-101 induced impairment of chk2 downstream DNA repair pathway and anti-proliferative activity in ovarian cancer cell lines. Patient-derived tumour spheroid culture also showed anti-cancer activity of PHI-101 regardless of BRCA1 status [10]. Thus, PHI-101, a new Chk2 inhibitor, is expected to suggest a different treatment strategy for ovarian cancer, either alone or as a combination therapy. Therefore, we designed a phase I dose-escalation trial to evaluate the safety and tolerability of PHI-101 for platinum-resistant recurrent ovarian cancer.

## Methods/Design

### Trial design

Chk2 inhibitor for Recurrent EpitheliAl periToneal, fallopIan, or oVarian cancEr (CREATIVE) trial is a prospective, multi-centre, phase I dose-escalation study to determine the dose-limiting toxicity (DLT) and maximum tolerated dose (MTD) of PHI-101. This study was approved by each institutional review board of all participating institutions and funded by Pharos iBio Co., Ltd. (Gyeonggi-do, Republic of Korea). Four participating institutions are listed: Ajou University Hospital, Bundang Seoul National University Hospital, Seoul National University Hospital, and Seoul ST. Mary's Hospital.

The investigators will obtain the informed consent form from all participants before any screening examinations. As shown in Figure 1, study participants will be orally administered PHI-101 (2 to 12 tablets/day) at a predetermined dose cohort once daily each for one cycle (28 days), and DLT will be observed during the first cycle of each subject by the list depicted in Table 1. Participants will continue to take PHI-101 until the following termination criteria are met: radiologic progression or clinical progression; death; withdrawal of consent; unacceptable adverse event; dose interruption longer than four weeks. Dose adjustment is not allowed during the DLT observation period (cycle 1, 28 days). Although treatment-specific side effects are not known so far, we included possible side effects shown in preclinical study results depicted in Supplementary Table 2 to the DLT list. During the study period, concomitant medication to control symptoms other than tumours is permitted. However, any antineoplastic therapies other than the IP (surgery, radio(chemo)therapy, cytotoxic chemotherapy, targeted therapy, and immuno-oncologic drug) and alternative treatments (nonprescription drug, herb, or homoeopathy) will be prohibited.

**Fig. 1 Fig1:**
[figure not shown]
Study design schema. (Abbreviations: DLT, dose-limiting toxicity; EOT, end of treatment; PK, pharmacokinetic sampling)

**Table 1 Tab1:** Definition of dose limiting toxicity (DLT)

CTCAE Term	CTCAE version 5.0
**Hematological toxicity**	
Febrile neutropenia	grade ≥ 3
Neutrophil count decreased	grade ≥ 3 for > 7 days
WBC decreased	grade ≥ 3
Platelet count decreased	grade ≥ 3
	grade < 3 requiring blood transfusion
Anemia	grade ≥ 3
**Non-hematological toxicity**	
ECG QT corrected interval prolonged	grade ≥ 3
Nausea	grade ≥ 3 for > 7 days despite the adequate and optimal therapy
Tumor pain	grade ≥ 3 for > 7 days despite the adequate and optimal therapy
Vomiting	grade 3 for > 7 days despite the adequate and optimal therapy, or grade ≥ 4
Diarrhea or associated electrolyte abnormalities	grade ≥ 3 for > 2 days despite the adequate and optimal therapy
Fatigue	grade ≥ 3 for > 7 days
Anorexia	grade ≥ 3 for > 7 days
Hypophosphatemia, hypomagnesemia, or hypocalcemia	grade ≥ 3 for > 2 days despite the adequate and optimal therapy
Asymptomatic AST, ALT, ALP, or GGT	grade ≥ 3 for > 7 days
Baseline AST or ALT ≥ 2.5 to 5 X ULN in patients with confirmed liver metastases	AST or ALT > 8 X ULN for > 7 days
Baseline ALP ≥ 2 to 5 X ULN in patients with confirmed liver metastases	ALP > 8 X ULN for > 7 days
All the other ADRs excluding above	grade ≥ 3

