**Other toxicity**	
ADR with dose interruption (temporary discontinuation) of PHI-101 for > 4 weeks	

Abbreviations: ALP, alkaline phosphatase; ALT, alanine transferase; AST, aspartate transferase; CTCAE, Common Terminology Criteria for Adverse Events; ECG, electrocardiography; GGT, γ-glutamyl transferase; ULN, upper normal limit; WBC, white blood count.

The study scheme for the cohort assignment is described in Fig. 2 [11]. The accelerated dose escalation scheme, which assesses DLT in a single subject in each cohort, will be applied for this phase I study. This accelerated dose-escalation scheme will be sustained until adverse drug reaction related to investigational product (IP) same or greater than grade 2 occurs. If IP-related toxicity ≥ grade 2 does not occur, DLT can be assessed at the higher dose cohort according to the recommendation of the safety review committee (SRC). If IP-related toxicity ≥ grade 2 occurs, additional two subjects will be enrolled in the same dose cohort, and the study will be switched to the standard 3+3 scheme. If DLT is observed in > 1 out of 6 subjects in a specific cohort (χ) and DLT is observed in ≤ 1 out of 6 subjects in the cohort (χ-1) that is one level lower than the specific cohort, the one level lower cohort (χ-1) will be considered as MTD. The dose of PHI-101 will be escalated until MTD is determined, and if the MTD is not determined at the maximum planned dose, dose-escalation will be ended at that dose.

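### Table 1 leaves a brief grade 4 diarrhea or anorexia out of the DLT count, although grade 4 vomiting counts at any duration

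*Protocol article*

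**What the plan says.** All references are to the protocol article.

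- **Vomiting (Table 1, non-hematological toxicity):** "grade 3 for > 7 days despite the adequate and optimal therapy, or grade ≥ 4". Grade 3 has a duration limit; grade 4 or above has none.
- **Diarrhea:** the row is labelled "Diarrhea or associated electrolyte abnormalities" and counts at "grade ≥ 3 for > 2 days despite the adequate and optimal therapy".
- **Anorexia:** counts at grade 3 or above if it lasts more than 7 days. No separate grade 4 condition is given.
- **Catch-all row:** grade 3 or above at any duration, but only for "All the other ADRs excluding above".
- **Other toxicity:** "ADR with dose interruption (temporary discontinuation) of PHI-101 for > 4 weeks".
- **MTD rule (Trial design):** a level with more than 1 DLT in 6 subjects is too toxic. The level below is the MTD if it shows at most 1 in 6.
- **DLT window (Trial design):** cycle 1, 28 days.

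**The concern.** A condition of grade 3 or above includes grade 4. In the diarrhea and anorexia rows, the duration limit therefore also applies to a grade 4 event, and one that resolves within the limit is not a DLT. The vomiting row handles the same situation differently, so the table ranks related gastrointestinal toxicities inconsistently. It also ranks them out of order against unlisted terms: a short grade 3 reaction that the table does not name is a DLT, and a short grade 4 diarrhea is not.

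The DLT count is the primary endpoint and the only quantity in the MTD rule. With at most six subjects at a level, a single event can decide whether that level qualifies as the MTD. The Trial design section says that treatment-specific side effects are not yet known, so there is no basis for assuming that these events will not occur.

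**Working it through.** **1. The plan's own figure.** Sample size gives six cohorts of one to six subjects: 6 × 1 = 6 and 6 × 6 = 36, which agrees with the stated range of six to 36. The article gives no DLT rates.

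**2. Table 1 applied as a rule to drug-related events in cycle 1.**

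| Event | Condition in its row | DLT? |
|---|---|---|
| Vomiting, grade 4, 1 day | grade ≥ 4, any duration | yes |
| Diarrhea, grade 4, 2 days | grade ≥ 3 and > 2 days | no |
| Diarrhea, grade 4, 3 days | grade ≥ 3 and > 2 days | yes |
| Anorexia, grade 4, 7 days | grade ≥ 3 and > 7 days | no |
| Anorexia, grade 4, 8 days | grade ≥ 3 and > 7 days | yes |
| Unlisted reaction, grade 3, 1 day | catch-all, grade ≥ 3 | yes |

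**3. Other routes into the count.** The catch-all excludes terms already listed. Reading it as any grade ≥ 3 reaction that misses its own row would cancel every duration limit for drug-related events in the table, so that cannot be the meaning. The interruption row needs more than 4 weeks off drug, which a short event does not bring about by itself. A separate unlisted complication of grade 3 or above would count in its own right, but the diarrhea or anorexia would still not count.

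**4. Effect on the six-subject rule.** Only the stated rule is used, because Fig. 2 is not shown. Let p be the probability that a subject has a counted DLT. Then

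P(≤ 1/6) = (1 − p)^6 + 6p(1 − p)^5.

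Assume a true rate of 30% with brief grade 4 events included, and let some of those points go uncounted:

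- 0 points, p = 0.30: 0.1176 + 0.3025 = 0.420
- 1 point, p = 0.29: 0.1281 + 0.3139 = 0.442
- 2 points, p = 0.28: 0.1393 + 0.3251 = 0.464

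The increase in P(≤ 1/6), in percentage points, over a range of assumed true rates:

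| True rate | 1 point uncounted | 2 points uncounted |
|---|---|---|
| 25% | +2.4 | +4.8 |
| 30% | +2.2 | +4.4 |
| 33% | +2.0 | +4.1 |
| 40% | +1.6 | +3.2 |

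**5. A cohort at the boundary.** Suppose exactly 2 of 6 subjects have a DLT when brief grade 4 events are included, and a share s of DLT subjects have only such an event. The chance that the recorded count falls to at most 1/6 is 1 − (1 − s)²:

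- s = 1/30: 1 − (29/30)² = 6.6%
- s = 2/30: 1 − (28/30)² = 12.9%

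With s = 0 there is no effect.

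**The case against.** **A duration limit over all grades ≥ 3 is the table's usual form.** It appears for neutrophils, nausea, tumor pain, fatigue, electrolytes and asymptomatic liver enzymes, and vomiting is the exception. One exception may show only that the authors wrote the override where they wanted it. This stands as far as intent goes: the table does not prove a drafting slip. It does not explain why diarrhea and anorexia should differ from vomiting, and the article gives no reason.

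**The CTCAE scales are not reproduced.** This also stands. That diarrhea and anorexia have a grade 4 is an assumption here, which the sponsor can check against version 5.0. If either had none, the added words would do nothing. No claim is made for nausea, tumor pain or fatigue.

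**Other safeguards exist.** A related toxicity of grade 2 or above ends the single-subject phase, the safety review committee reviews adverse events, and treatment stops for an unacceptable one. These lower the practical risk, but none adds the event to the DLT count.

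**The DLT list drew on preclinical findings.** The article says that possible side effects in Supplementary Table 2 were included. The supplement is not shown, so whether it informed these two limits cannot be judged.

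**Why not the other rows?** A reader might infer that every row of this form is wrong, including "Asymptomatic AST, ALT, ALP, or GGT" and the liver-metastasis rows ("AST or ALT > 8 X ULN for > 7 days" and "ALP > 8 X ULN for > 7 days"). The documents do not support that. A 7-day window for symptom-free enzyme rises may be deliberate, and a symptomatic rise of grade 3 or above falls to the catch-all. The liver-metastasis rows use multiples of the ULN rather than grades, so a grade override there is a debatable trade-off. The electrolyte and neutrophil windows may also be intended.

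**Conclusion.** The point holds for diarrhea and anorexia. As written, a drug-related grade 4 event in either row that resolves within its limit is left out of the count that sets the MTD, and no other row brings it back.

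A reader might go further and infer that the trial is likely to select too high a dose. The article does not support that, because it gives no event rates and every rate used here is assumed. If such events are rare, the effect is small: about 1.6 to 4.8 percentage points in P(≤ 1/6) when 1 to 2 points of a 25% to 40% DLT rate go uncounted. A larger shift, such as 42.0% to 53.4% at a true rate of 30%, would need 5 of the 30 points, one sixth of all DLTs, to be brief grade 4 events in these rows. Nothing in the article suggests that.

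The result assumes that both terms have a grade 4 and that the affected subject has no other DLT in cycle 1. The case rests on an unexplained inconsistency in the primary endpoint's definition, not on a large expected bias. It is a cheap improvement.

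**What to change.** Word two rows of Table 1 in the vomiting format and keep the present limits for grade 3:

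- **Diarrhea:** grade 3 lasting more than 2 days under the same optimal-therapy condition as now, or grade ≥ 4 at any duration. Move the associated electrolyte abnormalities to a row of their own with the present criterion (grade ≥ 3 for more than 2 days despite therapy).
- **Anorexia:** grade 3 lasting more than 7 days, or grade ≥ 4 at any duration.

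Leave the asymptomatic liver-enzyme, liver-metastasis, electrolyte and neutrophil rows as they are.

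No extra data are needed, since grade and duration are already required to apply the table. Escalation becomes slightly more conservative, because a short, reversible grade 4 diarrhea or anorexia would count as a DLT. If the trial has started, this is a wording amendment, which Data monitoring and management allows only exceptionally and with written consent from all parties involved.

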**Other toxicity**	
ADR with dose interruption (temporary discontinuation) of PHI-101 for > 4 weeks	

Abbreviations: ALP, alkaline phosphatase; ALT, alanine transferase; AST, aspartate transferase; CTCAE, Common Terminology Criteria for Adverse Events; ECG, electrocardiography; GGT, γ-glutamyl transferase; ULN, upper normal limit; WBC, white blood count.

The study scheme for the cohort assignment is described in Fig. 2 [11]. The accelerated dose escalation scheme, which assesses DLT in a single subject in each cohort, will be applied for this phase I study. This accelerated dose-escalation scheme will be sustained until adverse drug reaction related to investigational product (IP) same or greater than grade 2 occurs. If IP-related toxicity ≥ grade 2 does not occur, DLT can be assessed at the higher dose cohort according to the recommendation of the safety review committee (SRC). If IP-related toxicity ≥ grade 2 occurs, additional two subjects will be enrolled in the same dose cohort, and the study will be switched to the standard 3+3 scheme. If DLT is observed in > 1 out of 6 subjects in a specific cohort (χ) and DLT is observed in ≤ 1 out of 6 subjects in the cohort (χ-1) that is one level lower than the specific cohort, the one level lower cohort (χ-1) will be considered as MTD. The dose of PHI-101 will be escalated until MTD is determined, and if the MTD is not determined at the maximum planned dose, dose-escalation will be ended at that dose.

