#### Secondary objectives

Secondary objectives include assessing the IP tolerability by dose interruption, dose reduction, and dose termination due to adverse events. In addition, IP safety will be assessed by treatment-emergent adverse events, adverse drug reactions, serious adverse events, serious adverse drug reactions, and adverse events leading to withdrawal. Adverse events are defined as any unfavourable and unintended sign, symptom, or disease during the study period. Adverse events will be assessed according to the Common Terminology Criteria for Adverse Events (CTCAE) version 5.0 criteria. Also, physical examination, laboratory tests, vital signs, electrocardiogram will be performed for safety evaluation, and the investigators, including physicians and coordinating research nurse, will assess the adverse events for every visit.

Pharmacokinetic assessment will be done on cycle 1 day 1 (pre-dose, 0.5-, 1-, 2-, 4-, 6-, 8- and 24-hours post-dose), day 8 (pre-dose), day 15 (pre-dose, 0.5-, 1-, 2-, 4-, 6-, 8- and 24 hours post-dose), day 22 (pre-dose), cycle 2 day 1 (pre-dose and 2-4 hours post-dose), cycle 2 day 1 (pre-dose and 1-3 hours post-dose), and then every three cycles on day 1 to end of treatment (EOT). For pharmacokinetic analysis of PHI-101, 6mL of blood will be collected using a K2 EDTA tube and then centrifuged at 2,000g at 4°C for 10 minutes. The separated supernatant (plasma) will be dispensed into two tubes by 1mL or more and stored in a freezer at -70°C or lower.

Genetic variation, including HRD related genes including BRCA mutation based on tumour next-generation sequencing test results, will be collected for exploratory assessment. Additional biopsy or sequencing is not mandatory for the participants, but previously performed analysis results based on medical records will be analysed. For the efficacy assessment, a radiologic tumour response assessment will be done based on RECIST version 1.1.

The participants will be required to write a drug diary to improve adherence. Adequate and optimal supportive care will be permitted during the study, and therapies that may affect the efficacy and safety assessment of IP will be prohibited.

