### Statistical method

Safety analysis will be done on the subjects who received at least a single dose of the IP, and the number of events will be presented using the number of events by cohort. In addition, the DLT assessment will be done on the subjects who received at least a single dose of the IP and had DLT assessments during cycle 1. PK parameters including C_max_, C_max,ss_, C_min,ss_, C_av,ss_, AUC_t_, AUC_τ_, AUC_inf_, T_max_, T_max,ss_, t_1/2_, peak-trough fluctuation (PTF), accumulation ratio (AR), CL/F, CL_ss_/F, and V_z_/F will be calculated.

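### The DLT criterion of a dose interruption longer than 4 weeks cannot be met within the 28-day DLT observation period

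*Protocol article*

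**What the plan says.** The *Trial design* section of the protocol article sets the window: "DLT will be observed during the first cycle of each subject by the list depicted in Table 1". It gives the length of that window where it rules out changes to the dose: "Dose adjustment is not allowed during the DLT observation period (cycle 1, 28 days"). PHI-101 is taken once daily.

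The last row of Table 1, under *Other toxicity*, defines one DLT as "ADR with dose interruption (temporary discontinuation) of PHI-101 for > 4 weeks". *Trial design* uses the same threshold a second time, as a reason to end treatment: "dose interruption longer than four weeks".

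Three other provisions bear on the point:

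- Table 1 has a catch-all row, "All the other ADRs excluding above", which applies from grade 3 upwards.
- *Statistical method* defines the DLT-evaluable set as "subjects who received at least a single dose of the IP and had DLT assessments during cycle 1".
- *Secondary objectives* includes "assessing the IP tolerability by dose interruption, dose reduction, and dose termination due to adverse events".

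**The concern.** A DLT criterion has to be capable of being met in the period in which DLTs are counted. Here the required interruption is longer than the whole period, so the row has no effect on a literal reading.

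This matters because DLT and MTD are the primary endpoint, and the MTD rule turns on whether more than 1 of 6 subjects has a DLT. It is also the only Table 1 row that counts inability to keep taking the drug. A subject who takes very few doses, stops for a persistent grade 2 ADR and attends the cycle 1 assessments appears to meet the evaluable-set definition. Unless the full protocol has an exposure or replacement rule, that subject could count as a non-DLT at a dose that was hardly taken.

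**Working it through.** **Inputs.** DLT window: 28 days, first dose on day 1, once daily (*Trial design*). Threshold: more than 4 weeks, that is more than 4 × 7 = 28 days, so at least 29 missed days (Table 1). The plan gives no figure of its own on this point to reproduce.

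**Can the row be met by day 28?** Let *d* be the first missed day, from 2 to 28.

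- Missed days inside the window: 28 − *d* + 1. The largest value is at *d* = 2: 28 − 2 + 1 = 27.
- Day on which the 29th missed day falls: *d* + 28. For *d* = 2 this is day 30; for *d* = 28 it is day 56. The row is therefore first met 30 − 28 = 2 to 56 − 28 = 28 days after the window closes.
- Even if counting starts on day 1 itself, the maximum is 28 days, which is not more than 28.

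**Is this true of other rows?** Eleven other rows carry a duration condition:

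- More than 7 days (9 rows): neutrophil count, nausea, tumour pain, grade 3 vomiting, fatigue, anorexia, asymptomatic liver enzymes, and the two liver-metastasis rows. Onset on day *d* meets this by day 28 if *d* + 7 ≤ 28, so up to day 21.
- More than 2 days (2 rows): diarrhoea and the electrolyte row. The condition is *d* + 2 ≤ 28, so onset up to day 26.

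Only the interruption row fails for every start day.

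**Comparison with shorter thresholds.** A hold of more than *k* days is met by day 28 if *d* + *k* ≤ 28. The last column is the fewest cycle 1 doses a subject with one hold can take without meeting the row by day 28, for a hold that starts early enough to be judged.

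| Threshold | Start days that can meet it by day 28 | Fewest doses without a DLT on this row |
|---|---|---|
| > 28 days (as written) | 0 of 27 | 28 − 27 = 1 of 28 (4%); no hold can be judged |
| > 14 days | *d* = 2 to 14: 13 of 27 | 28 − 14 = 14 of 28 (50%) |
| > 7 days | *d* = 2 to 21: 20 of 27 | 28 − 7 = 21 of 28 (75%) |

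**Which holds go uncounted?** An ADR of grade 3 or higher in a row without a duration condition, or in the catch-all, is a DLT however early it resolves. Long holds that no row counts are those for:

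1. grade 1–2 ADRs, other than a platelet decrease requiring transfusion;
2. listed events of grade 3 or higher (for vomiting, grade 3) that do not last as long as their row requires;
3. liver-enzyme elevations in patients with liver metastases that do not reach the level in their row.

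**If the cycle 1 ban on dose adjustment also bars interruption,** no permitted hold can start in the window and the row is again empty.

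**The case against.** The day count is not in dispute; the argument is about how to read the rule. Table 1 may intend attribution by ADR onset: an event starting in cycle 1 is followed until it can be classified. Grade 3 neutropenia starting on day 25 cannot exceed 7 days by day 28 either, so the table already needs some rule for events that straddle the boundary. The shared threshold with the termination criterion also suggests that the row means an ADR that ends treatment through a prolonged hold, which can only be judged afterwards. Such a rule, like minimum exposure and replacement, may well be in the full protocol.

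There are safeguards too. In the accelerated phase, "If IP-related toxicity ≥ grade 2 occurs, additional two subjects will be enrolled in the same dose cohort" and the scheme changes to 3+3. Going to a higher dose after a subject without such toxicity follows the safety review committee's recommendation, and that committee also reviews adverse events periodically. If interruption is barred in cycle 1, the low-exposure case does not arise through a permitted hold.

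Much of this stands. Onset attribution is a plausible intention, the residual group is small, and the safeguards limit the harm. But the article states a 28-day observation period and does not state onset attribution. The other duration rows work for most onset days; this one works for none. The grade 2 trigger adds subjects but not a DLT, and interruptions reported as secondary tolerability data are not said to enter the DLT count. Two stated rules that do not fit together are different from detail left to a fuller document.

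**Conclusion.** The concern holds. As written, the interruption row cannot be met in the DLT period: 27 missed days are possible and 29 are needed. This rests on once-daily dosing from day 1 and on taking the stated 28-day period literally; it would not hold if DLTs are attributed by onset and followed past day 28, which the article neither states nor excludes.

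The practical reach is limited to the three kinds of hold listed above. The document gives no rate for them, so the effect on escalation or the MTD cannot be sized. It should still be corrected, because the row belongs to the primary endpoint and the repair is a matter of wording.

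**What to change.** Choose one of two wordings.

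1. **Keep the threshold and state the attribution rule.** Say that DLTs are attributed by ADR onset in cycle 1, that an ADR-related interruption ongoing at day 28 is followed until the criterion can be judged, and that escalation waits meanwhile. This removes the inconsistency without changing what counts as a DLT. Cost: a delay of 2 to 28 days, only when such a hold is ongoing at day 28.
2. **Replace the threshold with one observable in cycle 1.** Examples are an ADR-related interruption of more than 7 days, the duration already used in nine Table 1 rows, or more than 14 days. The sponsor and the safety review committee should set the figure. Cost: no delay, but somewhat more events count as DLTs. Holds starting after day 21 (for > 7 days) or day 14 (for > 14 days) still cannot be judged by day 28.

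The first is sufficient to cure the defect; the second is partly a choice about how strict the DLT definition should be.
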